### Data analysis plan

The primary objective is assessment of feasibility. This will focus on recruitment and retention rates, compliance, change in BPV and safety of the intervention. Exploratory analysis of the effect of the proposed intervention on BPV and stroke outcome will be done as a secondary objective.

#### Recruitment and retention

The total numbers of patients screened, the proportion recruited and the proportion completing follow-up will be determined. Reasons for ineligibility, non-inclusion and withdrawal will be analysed using descriptive statistical methods.

#### Assessment of the intervention

Compliance with the intervention will be assessed by the proportion of participants who achieve ≥80% adherence to the trial medication and the proportion of participants who have all BP measurements recorded successfully.

The feasibility of detecting changes in BPV will also be assessed. Within-individual systolic, diastolic and mean BPV will be expressed as the SD, coefficient of variation, average real variability and variation independent of the mean calculated from all BP measurements: enhanced casual, beat-to-beat measurements (each 10 min recording and the total 30 min recording), and daytime ABPM.^42^ Changes in within-individual BPV from baseline to the follow-up time points will be analysed using a general linear model. The size of the mean difference will be estimated for each approach and compared to select the most appropriate measure for a future study.

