## Methods and analysis

### Study overview

This study is a randomised, multicentre, open-label parallel group study to determine the feasibility of conducting such a trial in a National Health Service (NHS) setting to investigate class effects of antihypertensive medications on BPV in patients with acute ischaemic stroke or TIA. The aim is to evaluate barriers to recruitment, identify potential safety issues and demonstrate that it is possible to detect differences in BPV over the proposed study duration. We also hope to investigate the potential therapeutic benefit of targeting BPV after acute ischaemic stroke/TIA in terms of functional outcome in order to help estimate the necessary sample size for a future definitive trial. A summary of the study design is provided in figure 1. Recruitment commenced in January 2018 and is ongoing. The trial was prospectively registered: International Standard Randomised Controlled Trial Number 10853487.

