#### BP measurements

Baseline casual BP will be calculated as a mean of two sets of three supine brachial BP readings taken 10 min apart using a UA767 BP monitor (referred to as enhanced casual BP).

Three consecutive periods of 10 min beat-to-beat non-invasive BP monitoring in the supine position using the middle finger of the non-hemiparetic hand will be recorded with a Finometer device. The servo adjust mechanism of the Finometer will be switched off during the recording period, but applied at 10 min intervals during the monitoring period.

Daytime ambulatory BP monitoring (ABPM) will be performed using a SpaceLabs 90207 monitor, programmed to measure BP at 20 min intervals. Daytime is defined as between 07:00 and 22:00 hours.

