#### Secondary feasibility outcome measures

Changes in BPV from baseline to 21 (±7) days and 90 (±14) days by treatment arm.Proportions of participants achieving ≥80% treatment compliance by treatment arm.Treatment discontinuation rates.Completion and failure rates of BPV measurements at 21 (±7) days and 90 (±14) days.SAE rates by treatment arm.

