### Sample size calculation

A feasibility study of 150 patients (64 patients per group with a 15% dropout rate) will have an 80% power at the 5% significance level of detecting an 8 mm Hg difference in systolic BPV between the CCB and ACEI/ARB-based regimes, assuming a mean systolic BPV SD of 14.97 mm Hg in the CCB arm and 16.95 mm Hg in the ACEI/ARB arm.^37^

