#### Exploratory analyses

Mean BP will be calculated from enhanced casual measurements. Change in mean BP from baseline to follow-up by treatment arm will be compared using an independent samples t-test.

An assessment of treatment effect on BPV will be undertaken stratified according to treatment arm. A general linear model will be used with BPV as the dependent variable and treatment arm as the independent variable, adjusting for baseline BP and diagnosis (stroke vs TIA). Each expression of BPV as described above will be analysed.

Exploratory assessment of treatment effect on stroke outcome will be undertaken by comparing between-group differences in mRS and MoCA score at follow-up using independent samples t-tests or a non-parametric test if the assumptions of the t-test are violated.

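### The rule for choosing a BPV measure for a future study compares the size of mean differences across candidates that share neither a unit nor a spread

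*Protocol article*

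**What the plan says.** Under Assessment of the intervention, the protocol article lists the forms that BPV will take: "Within-individual systolic, diastolic and mean BPV will be expressed as the SD, coefficient of variation, average real variability and variation independent of the mean". These are computed from "enhanced casual, beat-to-beat measurements (each 10 min recording and the total 30 min recording), and daytime ABPM". Changes from baseline go into a general linear model, and then comes the selection rule: "The size of the mean difference will be estimated for each approach and compared to select the most appropriate measure for a future study".

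Under Exploratory analyses, a general linear model compares the arms, adjusted for baseline BP and for stroke versus TIA, and "Each expression of BPV as described above will be analysed". Secondary feasibility outcome measures include "Changes in BPV from baseline to 21 (±7) days and 90 (±14) days by treatment arm" and, separately, completion and failure rates of the BPV measurements. The selection sentence does not refer to those rates.

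**The concern.** The only criterion named for the choice is the size of a mean difference. A difference in mm Hg, one in percentage points and one on a fitted scale cannot be put in order by size. Even within one unit, a recording method with larger spread gives larger differences, both true and random, without being better at separating the arms. Taking the most striking of many correlated results also favours whichever was lifted by chance.

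At stake is which BPV measure a later study adopts. Followed as written, the rule could prefer a measure for its unit or its noise over one that detects a drug-class effect more reliably. The article states this rule itself, so the matter is not one of detail left to an analysis plan.

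**Working it through.** **Inputs from the protocol article.** Three BP components and four indices (Assessment of the intervention). Six recordings: casual, ambulatory, the 30 min total and each 10 min period, of which there are three ("Three consecutive periods of 10 min beat-to-beat non-invasive BP monitoring in the supine position", BP measurements). Ambulatory monitoring is scheduled at baseline and day 90 but not at day 21 (Table 1). Sample size: "A feasibility study of 150 patients (64 patients per group with a 15% dropout rate", a difference of 8 mm Hg, SDs of 14.97 and 16.95 mm Hg, 80% power and the 5% level.

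**The plan's own figure.** Root mean square SD = √((14.97² + 16.95²)/2) = 15.99, so the standardised difference is 8/15.99 = 0.50. A two-sided t-test calculation gives 64 per group (power 0.802). With dropout, 128/0.85 = 151, against 150 stated. The figure reproduces, and this point does not touch it.

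**Number of candidates.**
- Day 90: 3 × 4 × 6 = 72, of which 4 × 6 = 24 are systolic.
- Day 21, without ambulatory monitoring: 3 × 4 × 5 = 60, of which 20 are systolic.
- Both visits: 132.
- If *approach* means only the recording method: three (casual, beat-to-beat, ambulatory). If it means only the index: four.

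**Units.** With mean BP equal in both arms, the difference in CV = 100 × (difference in SD)/(mean BP). Mean BP at follow-up is not given, so I assume a range. For a 2 mm Hg difference in systolic SD:

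| Assumed mean systolic BP (mm Hg) | Difference in CV (points) |
|---|---|
| 130 | 1.54 |
| 150 | 1.33 |
| 170 | 1.18 |

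The effect is the same in every row, but by size the SD always ranks above the CV. Variation independent of the mean can be made larger or smaller by its scaling constant.

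**Spread.** If a measure has between-patient SD *s* and true standardised effect *d*, its expected raw difference is *d* × *s*. With 64 per arm, its standard error is *s* × √(2/64) = 0.177 *s*. With equal *d*, ranking raw differences is ranking *s*. With *d* = 0, the expected absolute difference is √(2/π) × 0.177 *s* = 0.141 *s*, so the noisier measure still tends to look larger.

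**Chance, after the unit problem is removed.** Suppose that K standardised between-arm differences have the same true value and common correlation ρ, and that the largest is taken. Its expected excess over the truth is E(K) × 0.177 × √(1 − ρ), where E(K) is the mean of the largest of K independent standard normal values. The document gives no correlations, so each ρ is an assumption.

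| Candidates | E(K) | Assumed ρ | Expected excess (SD units) |
|---|---|---|---|
| 3 (methods) | 0.846 | 0.2 to 0.5 | 0.13 to 0.11 |
| 4 (indices) | 1.029 | 0.85 | 0.07 |
| 24 (systolic, day 90) | 1.948 | 0.5 / 0.8 / 0.9 | 0.24 / 0.15 / 0.11 |
| 72 (all, day 90) | 2.388 | 0.5 / 0.8 / 0.9 | 0.30 / 0.19 / 0.13 |

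A simulation with 64 per arm and 20,000 runs agrees with the lower two rows. It also shows that, with no true effect and 72 candidates, at least one p < 0.05 occurs in about 71%, 33% and 21% of trials at ρ = 0.5, 0.8 and 0.9.

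These figures describe selection on standardised differences. They show what remains once units are dealt with and why a short list helps. They do not measure the bias from ranking raw sizes.

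**The case against.** The sentence does not say that the differences will be left unstandardised, nor that the largest wins; it says that they will be compared to find the most appropriate measure. It follows a sentence on change from baseline, so the mean difference could be change over time, in which case the standard error used above does not apply. *Approach* may mean three recording methods and not 72 combinations. Completion rates are collected and could be weighed in a fuller document. The BPV effects are declared exploratory, and the primary outcome is recruitment and retention.

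These points limit the size of the concern. They do not remove it: size is the only criterion stated, it is applied to quantities without a common unit, and doubt over which difference is meant is itself a reason to rewrite the sentence.

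A reader might go further in two ways, and the document supports neither.

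- *The rule will make the definitive trial too small.* Study overview does speak of using results "in order to help estimate the necessary sample size for a future definitive trial", but the words just before tie this to functional outcome, and Study objectives proposes the day-90 modified Rankin Scale as the primary exploratory outcome. Nothing carries the selected BPV difference into a sample size.
- *Having many candidates voids the stated 80% power.* The sample size calculation concerns one systolic BPV difference and reproduces. Exploratory comparison of several indices does not undo it.

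**Conclusion.** The concern holds as a flaw in a stated rule. Comparing the size of mean differences across SD, average real variability, CV and variation independent of the mean, and across recordings of different spread, partly ranks units, noise and chance. The unit and spread parts follow from the definitions; only the illustrative BP levels are assumed. The chance part depends on the correlations and on how *approach* is read: an expected excess of about 0.07 to 0.13 SD with three or four candidates, and about 0.13 to 0.30 SD with 72, under equal true effects and selection of the largest. That optimism would matter for planning only if the selected difference were later reused, which the article does not propose.

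Severity is should-fix: the choice of measure belongs to a secondary feasibility and exploratory aim, and no primary conclusion depends on it.

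**What to change.** Rewrite the selection sentence so that it:

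1. says that the differences compared are the between-arm differences from the adjusted general linear model;
2. puts them on a unit-free scale, the adjusted difference divided by the model's residual SD, each with a 95% confidence interval;
3. limits the comparison to a short prespecified list of systolic candidates (index, recording method and visit), with the rest descriptive;
4. considers them together with the completion and failure rates already listed as an outcome and, for beat-to-beat BP only, repeatability across the three 10 min recordings. No comparable within-visit repeat is described for ambulatory monitoring, so repeatability should not be the main criterion for all candidates;
5. states that the observed difference of the selected measure will not be used unadjusted as a planning effect.

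The cost is plan wording and slightly more analysis, with no new data. The article describes recruitment as ongoing, so the change is best made before any comparison by arm is seen.

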#### Safety

Rates of SAEs, including recurrent stroke/TIA, other cardiovascular events, death and hospitalisation, will be recorded up to 3 months. A descriptive comparison will be undertaken to compare the rates, but no formal hypothesis testing will be undertaken.

#### Exploratory analyses

Mean BP will be calculated from enhanced casual measurements. Change in mean BP from baseline to follow-up by treatment arm will be compared using an independent samples t-test.

An assessment of treatment effect on BPV will be undertaken stratified according to treatment arm. A general linear model will be used with BPV as the dependent variable and treatment arm as the independent variable, adjusting for baseline BP and diagnosis (stroke vs TIA). Each expression of BPV as described above will be analysed.

Exploratory assessment of treatment effect on stroke outcome will be undertaken by comparing between-group differences in mRS and MoCA score at follow-up using independent samples t-tests or a non-parametric test if the assumptions of the t-test are violated.

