### Study objectives

The primary objective of this study is to determine the feasibility of recruiting patients with acute stroke and TIA into an interventional randomised trial comparing the effect of different antihypertensive medication regimens on BPV.

Secondary feasibility objectives are:To determine the viability of measuring changes in BPV from baseline to 21 (±7) days and 90 (±14) days by treatment arm.To assess compliance rates with BPV measurement methods.To assess compliance rates with the investigational treatments.To identify serious adverse events (SAE) associated with the interventions, including recurrent stroke/TIA, other cardiovascular events, death and hospital readmission up to 3 months.

In addition to the feasibility objectives, exploratory outcomes that may be used in a future definitive RCT will be investigated. The proposed primary exploratory outcome will be modified Rankin Scale (mRS) score at day 90.

Exploratory secondary outcomes are:mRS at day 21.National Institutes of Health Stroke Scale (NIHSS) at day 21.Mean BP at day 21 and day 90.BPV at day 21 day and 90.Montreal Cognitive Assessment (MoCA) score at day 90.

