### Randomisation

After the baseline assessments eligible patients will be randomised using a computer-generated protocol, in blocks of 4, to a dihydropyridine CCB or ACEI/ARB-based regime. The study treatment will be dispensed at the baseline visit, but treatment will not be commenced within 48 hours of the qualifying event in keeping with current recommended practice. The actual therapeutic agent used will be at the discretion of the treating clinician, but dictated by the class of therapy that the participant is assigned to. Prescription of the medication will be done by the treating clinician and the initial supply will be dispensed by the treating hospital or community pharmacy in accordance with the hospital’s policy for providing discharge or outpatient medication. Further supplies will be provided by the participant’s GP. Unblinding will not be necessary as there is an open-label study design.

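### Mean BP and MoCA are compared without baseline adjustment, although both are measured before randomisation; the tests are valid but usually less precise than the model already planned for BPV

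*Protocol article*

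**What the plan says.** The Exploratory analyses section names the test for each outcome.

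- Mean BP, from enhanced casual readings: "Change in mean BP from baseline to follow-up by treatment arm will be compared using an independent samples t-test".
- MoCA, together with mRS: "comparing between-group differences in mRS and MoCA score at follow-up using independent samples t-tests or a non-parametric test", the second option applying if the t-test's assumptions fail. Study objectives lists the outcome as "Montreal Cognitive Assessment (MoCA) score at day 90".
- BPV: a general linear model with treatment arm, "adjusting for baseline BP and diagnosis (stroke vs TIA").

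Baseline values exist for both measures in question. The BP measurements section says "Baseline casual BP will be calculated as a mean of two sets of three supine brachial BP readings taken 10 min apart", and Table 1 repeats enhanced casual BP at both follow-up visits. Table 1 also marks MoCA at baseline and at 90 days. The Randomisation section places these measurements before allocation: "After the baseline assessments eligible patients will be randomised using a computer-generated protocol, in blocks of 4".

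**The concern.** The protocol fixes two analyses that use the baseline value inefficiently. Subtracting it in full, as a change score does, amounts to assuming a slope of 1 between baseline and follow-up. Ignoring it, as the MoCA comparison does, amounts to assuming a slope of 0. A linear model estimates the slope instead. The section gives no reason for adjusting BPV but neither of these two outcomes.

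Precision is at stake, and so is exposure to chance imbalance. The arms may differ at baseline, and the only allocation detail given is blocks of 4, with no balancing on BP or MoCA. The Study overview hopes that the data on functional outcome will help size a definitive trial, and Study objectives lists mean BP and MoCA among the outcomes that such a trial may use. Wider intervals than necessary make the data less useful for that choice.

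**Working it through.** **The plan's own figure.** The Sample size calculation gives "150 patients (64 patients per group with a 15% dropout rate") for "80% power at the 5% significance level", with a difference of 8 mm Hg in systolic BPV and SDs of 14.97 and 16.95 mm Hg. Taking the test as two-sided (not stated):

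- Pooled SD = √[(14.97² + 16.95²)/2] = 15.99.
- Normal approximation: n = 2 × [15.99 × (1.96 + 0.84)/8]² = 62.7, so 63 per group.
- Noncentral t: 64 per group gives 80.2% power (63 gives 79.6%).
- Dropout: 128/0.85 = 150.6, so 151; conversely 150 × 0.85 = 127.5 completers.

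The stated figures reproduce. They concern BPV, not mean BP or MoCA; only the 64 per arm is carried forward.

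**Variance of the treatment contrast.** Let r be the baseline-to-follow-up correlation and k the ratio of baseline SD to follow-up SD. Relative to the follow-up score alone, in large samples:

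- follow-up only: 1
- change score: 1 + k² − 2rk, which is 2(1 − r) when k = 1
- baseline-adjusted: 1 − r²

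The change score exceeds the adjusted variance by (k − r)², and follow-up only exceeds it by r². Neither can be negative, so the direction does not depend on k.

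**Size with equal SDs (k = 1).** The protocol gives no r, so the values below are assumed. The ratios to the adjusted variance are 2/(1 + r) for change and 1/(1 − r²) for follow-up only. Interval widths follow from their square roots. Power is for an effect that the adjusted analysis would detect with 80% power at 64 per arm.

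| r (assumed) | Change / adjusted (mean BP) | CI wider by | Power, change | Follow-up / adjusted (MoCA) | CI wider by | Power, follow-up |
|---|---|---|---|---|---|---|
| 0.3 | 1.54 | 24% | 62% | 1.10 | 5% | 76% |
| 0.5 | 1.33 | 15% | 68% | 1.33 | 15% | 68% |
| 0.7 | 1.18 | 9% | 73% | 1.96 | 40% | 52% |

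**Size with unequal SDs (mean BP).** The ratio is (1 + k² − 2rk)/(1 − r²).

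- r = 0.5, k = 0.7: 0.79/0.75 = 1.05.
- r = 0.5, k = 1.3: 1.39/0.75 = 1.85.
- r = 0.7, k = 0.7: 0.51/0.51 = 1.00. The slope r/k is 1, and the change score loses nothing.

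**Chance imbalance.** If the arms differ by D at baseline and the slope is b, the change-score estimate is shifted by (b − 1)D and the follow-up-only estimate by bD. For illustration, D = 3 mm Hg and b = 0.5 shift the mean BP estimate by 1.5 mm Hg in absolute size.

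**Cost of the adjustment.** Estimating one slope inflates the variance by about 1 + 1/(2 × 64 − 4) = 1.008. Allowing for this, adjustment still beats the follow-up score once r exceeds about 0.09 and, with equal SDs, beats the change score until r reaches about 0.98.

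**The case against.** The strongest reply is that nothing here is invalid. In a randomised comparison, a t-test on change or on follow-up scores is unbiased over randomisation and keeps its type I error. Both outcomes are exploratory in a feasibility trial, the sample size does not rest on either, and no decision rule uses them. All of that stands and limits how much weight the point carries.

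Four stronger readings are tempting, and the document does not support them.

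- A reader might infer that a change score must over-correct here, because patients enter with raised BP soon after onset, prior drugs are generally suspended and treatment is titrated to a target. These features make a slope below 1 plausible but do not establish it. Selection on BP above 130/80 mm Hg can narrow the baseline SD and bring the slope back towards 1; treating to target can do the opposite.
- A reader might infer that most of the MoCA variance could be removed. The share removed is r², which passes one half only when r exceeds about 0.71. At r of 0.3 and 0.5 it is 9% and 25%.
- A reader might infer that a class effect on BPV cannot be interpreted without a sharper mean BP contrast. The Abstract's remark about similar BP lowering describes prior evidence. The plan already includes the coefficient of variation and variation independent of the mean among its BPV measures.
- A reader might call the adjustment free. It needs no new data, but it uses a degree of freedom per covariate.

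It is also fair to object that simply replacing the tests would remove the non-parametric option for MoCA, a bounded score. That option ignores baseline too, but something should take its place.

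**Conclusion.** The point holds as one of efficiency, not validity. The protocol itself fixes the unadjusted tests, so this is not detail left to an analysis plan. In large samples, adjustment for the measure's own baseline is never less precise than either planned test, and at 64 per arm the small-sample cost of the slope is under 1% of variance. The size is uncertain because r is not given. Under equal SDs and assumed r from 0.3 to 0.7, the variance excess is 54% falling to 18% for mean BP, and 10% rising to 96% for MoCA. With unequal SDs the figure for mean BP runs from no excess to more than this. The primary feasibility conclusion is untouched; the change is worth making because it improves the exploratory estimates from data already being collected.

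**What to change.** For mean BP at days 21 and 90 and MoCA at day 90, replace the unadjusted tests with the general linear model already planned for BPV: follow-up value as outcome, treatment arm as factor, and the measure's own baseline value and diagnosis (stroke or TIA) as covariates. Report the adjusted difference with its 95% CI.

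If MoCA residuals clearly depart from normality, keep a fallback that still uses baseline, such as rank-based ANCOVA or bootstrap confidence intervals for the adjusted difference.

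The cost is a change of wording and about one degree of freedom per covariate. No extra patients, visits or measurements are needed.

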## Introduction

### Background

Raised blood pressure (BP) is common after acute stroke with at least 75% of patients having a systolic BP (SBP) >130 mm Hg at hospital admission^1 2^; SBP <130 mm Hg being the guideline target for secondary prevention following stroke.^3^ Increased poststroke BP is associated with poor prognosis^4 5^ and may result from raised intracranial pressure,^6^ increased sympathetic nervous system activity,^7^ abnormal baroreceptor sensitivity (BRS),^8^ haematoma expansion,^9^ cerebral oedema^10^ and a white-coat response.^11^ A spontaneous BP decrease usually occurs 4–10 days after ictus,^12^ but substantial BP reductions can be associated with cerebral hypoperfusion as a consequence of poststroke dysautoregulation.^13^ We have previously reported that both increased 24 hours and beat-to-beat BP levels following acute stroke are associated with a poor prognosis.^14–16^ Subsequently, data from the International Stroke Trial have suggested a U-shaped relation between baseline SBP (within 48 hours of stroke) and short-term (14-day mortality) and long-term (6-month death and dependency) outcomes; the lowest risk of death and dependency being at SBP 150 mm Hg.^17^ However, there is conflicting evidence regarding acute stroke hypertension treatment. Data from randomised controlled trials (RCT) suggest that BP can be safely reduced after the acute stroke period, however, there seems to be no indication that doing so is beneficial.^18–23^ Indeed, the Scandinavian Candesartan Acute Stroke Trial reported that it may actually be harmful, with a non-significant increased risk of poor 6-month functional outcome.^23^ Therefore, Cochrane meta-analysis and guidelines state that optimal BP management in the context of initial stroke management remains uncertain.^3 24–26^

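### The BPV treatment-effect model adjusts for baseline BP and diagnosis but omits the baseline value of the BPV index being analysed, which costs precision but does not bias the result

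*Protocol article*

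**What the plan says.** The Exploratory analyses section names the model for the treatment effect on BPV: "A general linear model will be used with BPV as the dependent variable and treatment arm as the independent variable, adjusting for baseline BP". The only other covariate is diagnosis, stroke or TIA. The model applies to every expression of BPV. Baseline BPV is not listed.

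The section Assessment of the intervention describes a second analysis: "Changes in within-individual BPV from baseline to the follow-up time points will be analysed using a general linear model". It names no covariates. The mean differences it yields are to be compared across indices and measurement methods to choose the measure for a later trial.

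Table 1 schedules enhanced casual, beat-to-beat and daytime ambulatory BP at baseline. The Randomisation section places baseline assessments before allocation. Change in BPV from baseline is itself a secondary feasibility outcome, so baseline BPV has to be computed in any case.

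**The concern.** When an outcome is also measured before randomisation, its own baseline value is usually the most useful covariate. Here the model uses BP level instead. Four indices are planned: SD, coefficient of variation (CV), average real variability and variation independent of the mean (VIM). CV and VIM are constructed to be less tied to BP level, so baseline BP probably explains least for those two.

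What is at stake is precision. The sample size is justified by power to detect a BPV difference between arms, and the estimated differences guide the choice of measure for a future study. Wider intervals than necessary weaken both uses. The indices and methods may also differ in how strongly baseline predicts follow-up. In that case an analysis without baseline BPV loses different amounts of precision for different measures, which muddies the comparison between them.

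**Working it through.** **Inputs from the Sample size calculation and Randomisation sections.** Effect and power: "will have an 80% power at the 5% significance level of detecting an 8 mm Hg difference in systolic BPV". Spread: "assuming a mean systolic BPV SD of 14.97 mm Hg in the CCB arm and 16.95 mm Hg in the ACEI/ARB arm". Numbers: "A feasibility study of 150 patients (64 patients per group with a 15% dropout rate". Allocation: "randomised using a computer-generated protocol, in blocks of 4, to a dihydropyridine CCB or ACEI/ARB-based regime"; equal allocation is inferred from the equal group sizes. These are taken at face value.

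**Step 1: reproduce the stated sample size.** Common SD = √[(14.97² + 16.95²)/2] = 15.99, so d = 8/15.99 = 0.50. Normal approximation, two-sided 5%: n = 2 × [15.99 × (1.960 + 0.842)/8]² = 62.7, so 63 per group. The t-based calculation gives 63.7, so 64. Power at 64 per group is 80.2% (t-test). For dropout, 128/0.85 = 150.6, so 151 against the stated 150. The figure reproduces, and it corresponds to a comparison of follow-up values with no covariate adjustment.

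**Step 2: variance under each analysis.** Let r be the baseline–follow-up correlation of a BPV index. The document gives no value, so r is assumed over a range. With equal SDs at both times, and follow-up variance set to 1:

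- follow-up only, no baseline information: 1
- adjusted for baseline BPV: 1 − r²
- change score without baseline BPV as covariate: 2(1 − r)

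Relative to adjustment, follow-up only costs 1/(1 − r²), and the change score costs 2(1 − r)/(1 − r²) = 2/(1 + r).

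**Step 3: results.** Power is for a two-sample t-test with 64 per arm and standardised difference 0.50/√(variance).

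| r (assumed) | Follow-up only: variance ratio | Change score: variance ratio | Power, follow-up only | Power, baseline BPV added | Power, change score without baseline BPV |
|---|---|---|---|---|---|
| 0.2 | 1.04 | 1.67 | 80% | 82% | 60% |
| 0.3 | 1.10 | 1.54 | 80% | 84% | 66% |
| 0.5 | 1.33 | 1.33 | 80% | 90% | 80% |
| 0.6 | 1.56 | 1.25 | 80% | 94% | 88% |

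**Step 4: what baseline BP recovers.** The planned model is not follow-up only, because it contains baseline BP and diagnosis. Suppose baseline BP correlates a with baseline BPV and relates to follow-up BPV only through it (both assumed). Its residual variance is then 1 − (a × r)². At r = 0.5:

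- a = 0.3: 1 − 0.15² = 0.978, power about 81%
- a = 0.5: 1 − 0.25² = 0.938, power about 83%
- baseline BPV in the model: 1 − 0.5² = 0.75, power about 90%

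Under these assumptions baseline BP recovers a minor part of the available gain. The contribution of diagnosis cannot be sized from the document.

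**Step 5: the change analysis.** Write change as follow-up minus baseline. If baseline BPV is a covariate, subtracting it from the outcome alters only its own coefficient (by −1). The arm coefficient and its standard error are identical to those of the follow-up model with the same covariates. The change-score columns in Step 3 therefore apply only if baseline BPV is left out.

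**The case against.** **Low stakes.** The primary outcome is recruitment and retention, and the BPV treatment effect is labelled exploratory. That stands and limits the severity. It does not remove the point, because the trial is sized on BPV and the BPV estimates are to inform a later trial.

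**The two losses are not large together.** At low r the follow-up model loses little (4% in variance at r = 0.2), while an unadjusted change score loses much. At high r the position reverses. This is correct. Under the equal-SD assumption, neither analysis beats adjustment for any r strictly between 0 and 1.

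**Adjusting for BP level is sensible.** The trial's rationale is that BPV matters independently of mean BP, and SD and average real variability are not corrected for the mean. This also stands: baseline BPV should be added to baseline BP, not put in its place.

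**Stronger readings that the document does not support.**

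- A reader might infer that chance imbalance in baseline BPV biases the comparison. Under randomisation it does not, and the standard error already allows for such imbalance.
- A reader might infer that the change analysis will run at 60% to 66% power. The protocol names no covariates for it, and a condensed article may leave them to the full plan.
- A reader might assume that r is below 0.5. No correlation is given, and the Rationale for the study only calls BPV reproducible.
- A reader might call the omission of days from onset an error, since entry extends to 7 days and the Background says "A spontaneous BP decrease usually occurs 4–10 days after ictus". That statement concerns BP level, not BPV, and the window lies before the scheduled day 21 and day 90 visits. Any gain is unquantified.

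**Conclusion.** The point holds as a loss of precision in a model whose covariates the protocol states explicitly. Against an analysis with no baseline information, adding baseline BPV raises power from about 80% to about 82%, 84% and 90% at r = 0.2, 0.3 and 0.5. The gain over the planned model is somewhat smaller, because baseline BP and diagnosis recover part of it. These figures rest on an assumed r, equal SDs at baseline and follow-up, and the protocol's own effect size and SDs.

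For the analysis of change in BPV the conclusion is conditional. Without baseline BPV as a covariate, its variance is 2/(1 + r) times that of the adjusted model. With it, and otherwise the same covariates, the arm effect is the same as in the adjusted follow-up model. Neither analysis is invalid, and the stated sample size is not in question.

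**What to change.** In Exploratory analyses, add the baseline value of the same BPV index, obtained by the same method, to the covariates, and keep baseline BP and diagnosis. In Assessment of the intervention, state that the between-arm BPV differences used to choose the measure come from this same model. Report the adjusted difference with its 95% confidence interval for each index and method. Days from onset may be added but is not required.

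The cost is a sentence in each of the two sections. No new measurement is needed, since every covariate is already scheduled at baseline, and the sample size need not change.
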